# 1. Title

A Randomized, Single-Blind, Placebo-Controlled Phase I Clinical Trial to Evaluate the Safety and Efficacy of Inhaled Extracellular Vesicle Therapy for Pulmonary Fibrotic Lesions

# 2. Objective

This study aims to assess the safety and efficacy of inhaled extracellular vesicle therapy in the treatment of patients with pulmonary fibrotic lesions.

**2.1. Primary Objective**

To evaluate the safety of inhaled extracellular vesicle therapy in patients with pulmonary fibrotic lesions as identified by high-resolution computed tomography (HRCT).

1. to monitor vital signs, clinical symptoms and signs, and the incidence of adverse events on Days 1–8, Week 4, and Week 12 after enrollment.
2. to assess changes in laboratory and clinical parameters on Day 8 and Week 12, including complete blood count, urinalysis (plus pregnancy test), blood biochemistry, electrocardiogram (ECG), peripheral oxygen saturation (SpO₂), tumor markers, levels of IL-6 and IL-10, immune cell function in peripheral blood, and lymphocyte subsets.

**2.2. Secondary Objectives**

1. to evaluate changes from baseline in pulmonary function on Days 4 and 8, Week 4, and Week 12;
2. to assess HRCT imaging changes from baseline at Week 4 and Week 12;
3. to evaluate changes from baseline in six-minute walk distance (graded and actual distance) on Days 4 and 8, Week 4, and Week 12 for patients meeting criterion 5.1.2 (2) for HRCT-defined fibrotic lesions;
4. to assess changes from baseline in the St. George’s Respiratory Questionnaire (SGRQ) on Days 4 and 8, Week 4, and Week 12;
5. to assess changes from baseline in the Leicester Cough Questionnaire on Days 4 and 8, Week 4, and Week 12;
6. to assess changes from baseline in the modified Medical Research Council (mMRC) Dyspnea Scale on Days 4 and 8, Week 4, and Week 12;
7. to monitor the frequency and severity of acute exacerbations in patients with HRCT-defined pulmonary fibrotic lesions from Days 1–8, Week 4, and Week 12.

# 3. Expected Outcomes Based on the previous results from cellular and animal studies and human safety evaluations from our group, and existing literature on the therapeutic effects of stem cells and extracellular vesicles, this study is expected to demonstrate that inhalation therapy with aerosolized extracellular vesicles derived from human umbilical cord mesenchymal stem cells can improve symptoms, quality of life, and pulmonary function in patients with pulmonary fibrotic lesions, alleviate lung fibrosis, and reduce the frequency of acute exacerbation events.

# 4. Study Design

**4.1. Overview of Study Design**

This is a phase I clinical trial, designed as a single-center, randomized (1:1), single-blind, placebo-controlled clinical study.

**4.2. Dose Selection**

Based on previous animal studies and clinical data, the selected dose for this study is designed as 2×10^9^ particles per nebulization, with administration twice daily for 7 consecutive days.

**4.3. Observation Items and Indicators**

4.3.1. Screening or Baseline Data

This includes medical records of the participants prior to the enrollment. After obtaining informed consent from the participants or their legal representative, investigators will review medical records to collect the following data：

- Basic information: demographic characteristics, height, and weight;
- Pre-enrollment diagnosis, medical history, and previous treatments;
- Treatment-related information: medications;
- Vital signs and comprehensive physical examination;
- Routine tests: complete blood count (CBC), urinalysis + pregnancy test, blood biochemistry, infectious disease screening, electrocardiogram (ECG), fingertip oxygen saturation, tumor markers, IL-6 and IL-10 levels, peripheral blood immune cell function, and lymphocyte subpopulations;
- Pulmonary function tests: percentage predicted of carbon monoxide diffusion capacity (DLco), forced vital capacity (FVC), and DLCO/VA;
- Six-minute walk test (graded and distance);
- SGRQ: St. George’s Respiratory Questionnaire;
- LCQ: Leicester Cough Questionnaire;
- mMRC Dyspnea Scale: Modified Medical Research Council Dyspnea Scale;
- Chest HRCT: Chest High-Resolution Computed Tomography.

4.3.2. Post-enrollment Observation Indicators

1. Specific indicators after enrollment (see Table 1):
   - Vital signs and comprehensive physical examination;
   - Routine tests: CBC, urinalysis, blood biochemistry, ECG, fingertip oxygen saturation, tumor markers, IL-6 and IL-10 levels, peripheral blood immune cell function, lymphocyte subpopulations;
   - Pulmonary function tests: percentage predicted of DLco, FVC, and DLCO/VA;
   - Six-minute walk test (graded and distance);
   - SGRQ;
   - LCQ;
   - mMRC Dyspnea Scale;
   - Chest HRCT;
   - Acute exacerbation events (frequency and severity).
2. Adverse events during the administration period of the investigational drug. If any adverse event occurs, the patient will be followed up until resolution or end of treatment. The occurrence time and severity of complications involving various organ systems (e.g., cardiac events, cerebrovascular events, infections, etc.) will be recorded;
3. For participants discharged or deceased after enrollment, record the death event, length of hospital stay, duration of mechanical ventilation, and total treatment cost;
4. Long-term observation indicators post-enrollment (up to 1 year):
   Considering the long-term safety concerns of exosome therapy, follow-up calls will be conducted at weeks 24 and 48 to record any adverse events for long-term safety assessment.

(see next page for Table 1)

Table 1. Schedule of Assessments

| Visit | Screening  -2d～0d | Baseline  D0 | D1 | D2 | D3 | D4 | D5 | D6 | D7 | D8 | D28  ±3d | D84  ±3d | D180  ±5d | D360  ±7d |
| --- | --- | --- | --- | --- | --- | --- | --- | --- | --- | --- | --- | --- | --- | --- |
| **Basic medical history** | | |  |  |  |  |  |  |  |  |  |  |  |  |
| informed consent | × |  |  |  |  |  |  |  |  |  |  |  |  |  |
| Demographic data | × |  |  |  |  |  |  |  |  |  |  |  |  |  |
| General clinical data | × |  |  |  |  |  |  |  |  |  | × | × |  |  |
| **Security assessment** | | |  |  |  |  |  |  |  |  |  |  |  |  |
| Vital sign | × | × | × | × | × | × | × | × | × | × | × | × |  |  |
| Physical examination | × | × | × | × | × | × | × | × | × | × | × | × |  |  |
| Blood routine examination |  | × |  |  |  |  |  |  |  | × |  | × |  |  |
| urinalysis |  | × |  |  |  |  |  |  |  | × |  | × |  |  |
| Urine pregnancy test (women of gestational age only) |  | × |  |  |  |  |  |  |  | × |  | × |  |  |
| Infectious disease screening |  | × |  |  |  |  |  |  |  |  |  | × |  |  |
| Blood biochemical examination |  | × |  |  |  |  |  |  |  | × |  | × |  |  |
| Tumor marker |  | × |  |  |  |  |  |  |  |  |  | × |  |  |
| IL-6 |  | × |  |  |  |  |  |  |  | × |  | × |  |  |
| Peripheral blood lymphocyte subsets |  | × |  |  |  |  |  |  |  | × |  | × |  |  |
| ECG |  | × |  |  |  |  |  |  |  | × |  | × |  |  |
| Finger oxygen saturation |  | × | × | × | × | × | × | × | × | × | × | × |  |  |
| **Effectiveness evaluation** | | |  |  |  |  |  |  |  |  |  |  |  |  |
| Chest HRCT |  | × |  |  |  |  |  |  |  |  | × | × |  |  |
| Lung function test |  | × |  |  |  | × |  |  |  | × | × | × |  |  |
| Lung diffusion function test |  | × |  |  |  | × |  |  |  | × | × | × |  |  |
| 6MWD |  | × |  |  |  |  |  |  |  | × | × | × |  |  |
| mMRC |  | × |  |  |  |  |  |  |  | × | × | × |  |  |
| SGRQ |  | × |  |  |  |  |  |  |  | × | × | × |  |  |
| LCQ |  | × |  |  |  |  |  |  |  | × | × | × |  |  |
| Acute aggravating event |  |  | × | × | × | × | × | × | × | × | × | × | × | × |
| AE/SAE |  |  | × | × | × | × | × | × | × | × | × | × | × | × |

IL-6=interleukin 6; ECG=electrocardiogram; HRCT=High Resolution Chest Tomography; 6MWD=Six - Minute Walk Distance；SGRQ=St. George's Respiratory Questionnaire；LCQ=**Cough-specific Quality of Life Questionnaire；**mMRC=Modified Medical Research Council；AE/SAE=**Adverse Event/Serious Adverse Event.**

The terms used in this section:

mMRC Dyspnea Scale

The Modified Medical Research Council (mMRC) Dyspnea Scale (Table 2) is a single-rating scale used to assess the degree of breathlessness. This 5-grade scale considers activities that may trigger dyspnea in patients, such as walking or climbing stairs. Patients are asked to select the grade that best describes their current level of breathlessness.

Table 2. mMRC Dyspnea Scale

| **Grade** | **Description of Dyspnea** |
| --- | --- |
| 0 | Not troubled by breathlessness except during strenuous exercise. |
| 1 | Short of breath when hurrying on level ground or walking up a slight hill. |
| 2 | Walks slower than people of the same age on level ground due to breathlessness, or has to stop for breath when walking at own pace. |
| 3 | Stops for breath after walking about 100 yards or after a few minutes on level ground. |
| 4 | Too breathless to leave the house or breathless when dressing or undressing. |

Leicester Cough Questionnaire (LCQ)

The LCQ is a 19-item questionnaire designed to evaluate cough-related quality of life. It uses a 7-point Likert scale to assess symptoms or their impact over the past 2 weeks. The LCQ covers three domains: physical (8 items), psychological (7 items), and social (4 items). Scores for each domain are calculated as the mean of the respective items (range: 1–7). A total score (range: 3–21) is obtained by summing domain scores. Higher scores indicate better quality of life.

St. George’s Respiratory Questionnaire (SGRQ)

The SGRQ is a 50-item patient-reported outcome (PRO) questionnaire developed to assess health status in patients with obstructive airway diseases. It has two parts: Part 1 includes 8 questions on respiratory symptom severity over the past 4 weeks; Part 2 includes 42 questions on daily activity limitations and psychosocial impact. The SGRQ generates a total score and three component scores (Symptoms, Activity, and Impacts). The total score reflects the overall impact of the disease on health status, expressed as a percentage from 0 (best health) to 100 (worst health). Similarly, component scores range from 0 to 100, with higher scores indicating greater impairment.

# 5. Eligibility Criteria and Group Allocation Method

**5.1.** **Inclusion Criteria**

1. Age between 18 and 80 years (inclusive), no gender restriction.
2. Meets HRCT criteria for pulmonary fibrotic lesions:
   - 1. Manifestations include linear, rigid high-density shadows or nodular high-density shadows in the lungs.
     2. Manifestations include diffuse reticular, linear, honeycomb-like shadows or reticulonodular shadows in both lungs.
3. Typical HRCT imaging features of pulmonary fibrotic lesions within the past 12 weeks, including idiopathic pulmonary fibrosis, COPD with fibrosis, and chronic cough caused by organizing pneumonia post-COVID-19 infection.
4. Able to understand and cooperate with the pulmonary function test procedures.
5. Fully informed about the purpose, methods, and possible discomfort of the trial, agrees to participate, and voluntarily signs the informed consent form.
6. Good compliance, willing to follow the medication regimen as required by the protocol and attend follow-up examinations on time.

**5.2. Exclusion Criteria**

1. Previous stem cell therapy.
2. Intolerance to nebulized inhalation therapy.
3. Allergic constitution or history of potentially life-threatening drug allergies.
4. Pregnant or planning to become pregnant soon, or breastfeeding women.
5. Male participants with reproductive potential and female participants of childbearing age unwilling to use effective contraception during the treatment period and for 12 months following the end of the follow-up.
6. History of malignant tumors or systemic anti-cancer treatment within 5 years prior to the screening period.
7. Active hepatitis B or C virus infection, or HIV infection.
8. History of organ transplantation or currently awaiting organ transplantation.
9. Underwent surgery (excluding diagnostic surgery) within 8 weeks prior to enrollment, planning to undergo surgery during the study period, or with an unhealed surgical wound prior to enrollment.
10. Taking or planning to take Nintedanib or Pirfenidone within the past month.
11. Any of the following lung diseases: bronchial asthma, active pulmonary tuberculosis, pulmonary embolism, pneumothorax, pneumoconiosis, idiopathic pulmonary arterial hypertension, obliterative bronchiolitis, or other active lung diseases.
12. Current or recent (within 4 weeks) pneumonia.
13. Previous lung resection surgery.
14. Currently requiring oxygen therapy for more than 15 hours per day.
15. History of mental illness, epilepsy, or other central nervous system diseases.
16. Severe other systemic diseases such as myocardial infarction, unstable angina, heart failure, liver cirrhosis, acute glomerulonephritis, etc.
17. Participation in any other clinical trial within 3 months prior to screening.
18. Currently participating in another clinical trial.
19. Poor compliance, making it difficult to complete the study.
20. Any condition that the researcher believes may increase the risk to the participant or interfere with the study results.

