**7.4. Course of Treatment**

One course lasts 7 days, and it will not be repeated.

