# 8 Criteria for Suspension and Termination of the Clinical Study

**8.1. Criteria for Participant Withdrawal or Study Termination**

1. The subject withdraws informed consent and requests to discontinue participation.
2. The subject exhibits significant non-compliance.
3. Occurrence of pregnancy, serious adverse events, death, or loss to follow-up.
4. Use of prohibited concomitant medications.
5. The subject fails to attend scheduled visits.
6. Investigators should make every effort to ensure that each subject completes the follow-up phase, unless discontinuation is clearly in the subject's best interest. Subjects who withdraw from the study should still enter the follow-up phase and will receive periodic follow-ups to monitor survival status until death or the end of the study.

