**12.1. Treatment Observation Period and Follow-up Methods**

Safety and efficacy observations will be conducted according to the study schedule. Additional safety follow-ups will be conducted via telephone visits at 6 and 12 months.

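### Exclusion 5 literally leaves contraception unrequired from Day 8 to an undefined end of follow-up, and exclusion 10 gives planned antifibrotic use a look-back window that cannot apply to a plan

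*Protocol*

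**What the plan says.** **Contraception.** Protocol section 5.2, exclusion 5, applies to men with reproductive potential and to women of childbearing age. It excludes those "unwilling to use effective contraception during the treatment period and for 12 months following the end of the follow-up". Section 7.4 fixes the treatment period: "One course lasts 7 days, and it will not be repeated".

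The end of follow-up is described in several ways. Table 1 has on-site assessments up to D84 and further contacts at D180 and D360. The text of section 4.3.2 says that "follow-up calls will be conducted at weeks 24 and 48". Section 12.1 says "Additional safety follow-ups will be conducted via telephone visits at 6 and 12 months".

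Table 1 schedules urine pregnancy tests at baseline, D8 and D84. Section 8.1(3) lists pregnancy among the grounds for withdrawal or termination.

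**Antifibrotics.** Exclusion 10 in the same list reads "Taking or planning to take Nintedanib or Pirfenidone within the past month". Exclusion 9, directly above it, treats surgery differently. It gives a look-back of 8 weeks and, separately, a forward criterion: "planning to undergo surgery during the study period". After enrolment, section 8.1(4) lists "Use of prohibited concomitant medications" as a ground for withdrawal. Section 5.4(3) removes from the final analysis a subject whose use of a prohibited drug made evaluation impossible. The protocol names no prohibited drug in either place.

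**The concern.** The two criteria fail in different ways.

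Exclusion 5 names one period that ends on Day 7 and another that begins only when follow-up is over. The interval in which the trial actually observes its participants lies between them. This is a participant-protection rule, and staff and participants will work from its wording. As written, it covers a year after the last contact but not the months before that contact. The protocol plainly cares about pregnancy after Day 7, since it tests for it at D8 and D84 and makes it a withdrawal ground.

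Exclusion 10 attaches a past window to a future intention. Two screeners could read it differently for the same patient. The question returns after enrolment: if a participant starts one of these drugs, sections 5.4(3) and 8.1(4) turn on whether it is prohibited, and the protocol does not say. That participant might stay in unchanged, be withdrawn with the last major efficacy assessment carried forward as the final result (section 5.3), or be removed from the final analysis (section 5.4). Pulmonary function and HRCT are listed as primary efficacy endpoints in section 9.1, so the handling matters for the comparison.

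**Working it through.** The protocol states no figure for either window, so there is nothing to reproduce. The check is a day count for exclusion 5 and a comparison of readings for exclusion 10.

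**Exclusion 5: inputs**
- Treatment: D1 to D7 (section 7.4, Table 1), so the first day not named is D8.
- Possible ends of follow-up: D84, the last on-site assessment in Table 1; week 48, from section 4.3.2; D360, the last column of Table 1. The 12-month call in section 12.1 corresponds to about D360.

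**Exclusion 5: formula.** Days not named = last day of follow-up − 8 + 1, using nominal days and ignoring visit windows.

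| End of follow-up | Last day | Days not named |
| --- | --- | --- |
| Last on-site visit | 84 | 84 − 8 + 1 = 77 |
| Week-48 call | 48 × 7 = 336 | 336 − 8 + 1 = 329 |
| Last contact in Table 1 | 360 | 360 − 8 + 1 = 353 |

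The gap is positive on every reading.

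**Does another provision close it?**
- Exclusion 4 rejects women who are pregnant, breastfeeding or planning pregnancy soon. It says nothing about men and imposes no contraception duty.
- The D8 and D84 pregnancy tests detect pregnancy; they do not require its prevention.
- Section 8.1(3) deals with what follows a pregnancy.

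None of these states a contraception requirement for the interval.

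**Exclusion 10: the two readings**
1. The past month governs both verbs. Current or recent use is caught. Planned use has no workable window, because a future start cannot fall in the past month.
2. The past month governs only taking. Planned use is then an exclusion ground with no stated horizon, so it is unclear whether a start intended after D84, or after D360, counts.

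Neither reading gives a forward period. Exclusion 9 does, by tying planned surgery to the study period, so the omission is particular to exclusion 10.

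**After enrolment.** Sections 5.4(3) and 8.1(4) both depend on a drug being prohibited. Neither names one or refers to exclusion 10, so they cannot be used to work out the missing forward window.

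**The case against.** **Exclusion 5.** The best defence is intent. A duty that runs to 12 months after follow-up was most plausibly meant to include follow-up, and the later pregnancy tests and the withdrawal ground fit that. This is fair as an account of what the drafters meant, and it is why the problem is probably a drafting gap. It does not change what the text requires. A reader might infer that exclusion 5 conflicts with the D84 pregnancy test or with section 8.1(3). It does not: both are compatible with contraception being expected after Day 7, and they show only that the interval matters. A reader might also take 353 days as the size of the gap, but that is the top of the range.

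**Exclusion 10.** The defence is stronger here. The criterion expressly names planned use as a ground for exclusion, and the second reading gives those words effect. Exclusion 20 also lets the investigator exclude anyone whose condition may interfere with the results. A reader might infer that patients planning an antifibrotic pass screening, leaving the whole efficacy period open to such use. The documents do not support that. What stands is the ambiguity and the risk of uneven application.

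Nor can harm to the efficacy comparison be quantified. The protocol gives no rate at which patients start these drugs and does not describe their effect on the outcomes. With 12 per arm, one patient is 1/12 = 8.3% of an arm, but that is true of any patient and is not an estimate of bias.

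**Conclusion.** The exclusion 5 limb holds on the literal text. The two required periods are not contiguous, and the uncovered interval is 77, 329 or 353 days depending on what ends follow-up. That the gap exists rests only on the 7-day course and on follow-up continuing past Day 7, both of which are stated. Its length rests on an undefined term.

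The exclusion 10 limb holds as a finding of ambiguity. The window does not fit planned use, no forward period is given, and the rules that apply after enrolment do not resolve it. No size can be attached to its effect.

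Both should be corrected. Exclusion 5 carries more weight because it concerns participant protection. Neither limb changes the sample size or the planned tests.

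**What to change.** - **Exclusion 5:** reconcile it with section 7.4, section 8.1(3) and Table 1, and state one continuous contraception window with a defined start and end. This requires defining the end of follow-up, and so aligning weeks 24 and 48 in section 4.3.2 with D180 and D360 in Table 1 and with the months in section 12.1.
- **Exclusion 10:** give recent use a look-back window and planned use a separate forward window, as exclusion 9 does for surgery. Reconcile the result with sections 5.4(3) and 8.1(4), so that it is clear whether these drugs count as prohibited after enrolment.

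The lengths of the windows, and which drugs are prohibited, are for the sponsor to decide. The cost is rewording two criteria and their cross-references. Depending on the windows chosen, there may be a few more screen failures.

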**5.3. Criteria for Early Withdrawal**

Subjects will be withdrawn from the study if they request to discontinue participation or withdraw informed consent (e.g., due to poor efficacy or adverse events), or are unable to comply with study requirements. Subjects may also be withdrawn at the discretion of the investigator if serious complications or comorbidities, or severe adverse events occur.

The reason for withdrawal must be thoroughly documented. The most recent major efficacy assessment before withdrawal will be used as the final result for statistical analysis. The subject’s CRF (Case Report Form) must be retained for future reference.

**5.4. Criteria for Exclusion from Analysis**

Subjects who have already been enrolled but meet any of the following criteria should be excluded from the final analysis:

1. The subject never received the investigational drug.
2. There are no valid assessment records.
3. The subject used a prohibited medication, making efficacy and safety evaluation impossible.

Reasons for exclusion must be stated clearly. Excluded cases will not be included in efficacy analyses. Their CRFs should still be preserved for future reference.

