**5.5. Group Allocation Method**

5.5.1. Randomization Method

Randomization codes in a 1:1 ratio for the treatment and placebo groups will be generated using the SAS statistical software package by a statistician who is not involved in data management or analysis. A block randomization design will be used, with each block including one subject in the exosome treatment group and one in the placebo group.

Drug assignment codes will be created by a statistician unaffiliated with the study. The randomization system will be available 24 hours a day. Investigational drugs will be administered according to the order of enrollment using corresponding random numbers.

The randomization codes (sealed blind codes) will be prepared in duplicate and securely stored by the principal investigator and the clinical trial pharmacy at the study institution.

Randomization and blinding will be guided by the Biostatistics Department of Hainan Medical University.

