# 6. Sample Size Requirement

This study is a randomized, placebo-controlled, exploratory clinical trial. A total of 24 subjects will be enrolled at the First Affiliated Hospital of Hainan Medical University, with 12 subjects assigned to the treatment group and 12 to the placebo group.

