# 11. Statistical Analysis of Study Results

**11.1. Dataset Definitions**

- 1. Full Analysis Set (FAS)

All randomized subjects, regardless of whether they received aerosolized EV treatment are included. Analysis will be conducted according to the Intention-To-Treat (ITT) principle.

- 1. Per-Protocol Set (PPS)

Randomized subjects who received at least one dose of the assigned aerosolized EV treatment and had no major protocol deviations, as well as control subjects who did not receive EV aerosol treatment are included. Criteria for exclusion from the PPS will be defined prior to database lock and will be detailed in the statistical analysis plan.

- 1. Safety Analysis Set (SAS)

Randomized subjects who received at least one dose of aerosolized EVs are included. This set will be used for all safety evaluations. Subjects who were not randomized but received the study treatment will have their safety data listed separately and used only for overall safety evaluation of the study treatment.

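### Section 5.4 excludes randomized subjects whom Sections 11.1 and 11.2 keep, and Section 5.3 fixes the last value before withdrawal as the final result

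*Protocol*

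**What the plan says.** Section 5.4 opens with "Subjects who have already been enrolled but meet any of the following criteria should be excluded from the final analysis". Its three criteria are no study drug received, no valid records, and "The subject used a prohibited medication, making efficacy and safety evaluation impossible". It adds that these cases stay out of the efficacy analyses.

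Section 11.1 defines the Full Analysis Set (FAS) as follows: "All randomized subjects, regardless of whether they received aerosolized EV treatment are included". Section 11.2 bases the primary and secondary efficacy reports on intention-to-treat. Section 11.1 also defines a separate Per-Protocol Set (PPS) for subjects without major deviations and defers only that set's exclusion criteria to the statistical analysis plan.

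Section 5.3 covers withdrawal at the subject's request, with poor efficacy and adverse events as examples, and withdrawal at the investigator's discretion for serious complications or severe adverse events. It then fixes the handling: "The most recent major efficacy assessment before withdrawal will be used as the final result for statistical analysis".

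Section 8.1 lists among its withdrawal or termination criteria "Occurrence of pregnancy, serious adverse events, death, or loss to follow-up", and also prohibited concomitant medication. It continues: "Subjects who withdraw from the study should still enter the follow-up phase and will receive periodic follow-ups to monitor survival status until death". Study completion is the other end point it names for this follow-up.

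**The concern.** Two separate problems affect who and what enters the efficacy comparison.

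First, Section 5.4 and Sections 11.1/11.2 give opposite instructions for the same subjects. Whichever rule is applied breaches the other, and the choice could be made after the data are seen. The third criterion of 5.4 matters most. Starting another drug happens after randomization, can follow from worsening, and leads to exclusion only if someone judges evaluation impossible. Section 4.1 calls the trial single-blind, and Section 7.1 has investigators sign for the vesicle product by subject name, so that judgement may not be blind to arm.

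Second, Section 5.3 makes carry-forward the fixed rule for people whose reason for leaving may be their outcome. Anything that happens to them after the last assessment is replaced by an earlier value. Section 8.1 does send them into follow-up, but the only purpose it names is survival status, so it is unclear whether later efficacy data would be collected. If they are, 5.3 sets them aside.

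Section 11.4 compares the proportion with disease progression between arms, and Section 11.2 tests at a two-sided 0.05 level. With 12 subjects per arm, a handful handled differently can change that comparison.

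**Working it through.** **1. The rules side by side**

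| Randomized subject | Section 5.4 | Sections 11.1 and 11.2 |
|---|---|---|
| Never treated | Out of final and efficacy analyses | In, explicitly |
| No valid records | Out | In |
| Prohibited medication judged to prevent evaluation | Out | In |
| Withdrew early, earlier assessment exists | Not excluded on this ground | In; 5.3 supplies the last earlier value |

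The first three rows conflict. The fourth does not: carry-forward decides which value is used, not who is in the set.

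**2. Inputs from the protocol**

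Section 6 gives 24 subjects, "with 12 subjects assigned to the treatment group and 12 to the placebo group". Section 5.5.1 gives "Randomization codes in a 1:1 ratio for the treatment and placebo groups". The check 12 + 12 = 24 agrees. No progression rate, effect size, power or withdrawal rate is stated, so every rate below is an assumption. One patient is 100/12 = 8.3 percentage points of an arm.

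**3. Fixed-count illustration (assumed)**

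Both arms truly have x progressors out of 12, and k of them in one arm are affected.

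- Deleted: false difference = x/12 − (x − k)/(12 − k).
- Scored as non-progressors: false difference = k/12.

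With x = 4:

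| k | Deleted | Scored as non-progressor |
|---|---|---|
| 1 | 4/12 − 3/11 = 6.1 points | 1/12 = 8.3 points |
| 2 | 4/12 − 2/10 = 13.3 points | 2/12 = 16.7 points |
| 3 | 4/12 − 1/9 = 22.2 points | 3/12 = 25.0 points |

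For k = 1, 2, 3, the deleted column becomes 6.8, 15.0 and 25.0 points with x = 3, and 4.5, 10.0 and 16.7 points with x = 6. The other column does not depend on x. The right-hand column represents subjects whose progression comes after they leave and is not counted.

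**4. Expected bias with no true effect (assumed)**

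Let p be the progression rate in both arms and q the share of progressors affected in an arm. The apparent rate is p(1 − q)/(1 − pq) if they are deleted and p(1 − q) if they are scored as non-progressors. With q = 10% in one arm and 40% in the other:

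| p | Deleted | Scored as non-progressor |
|---|---|---|
| 20% | 0.18/0.98 − 0.12/0.92 = 5.3 points | 0.18 − 0.12 = 6.0 points |
| 30% | 0.27/0.97 − 0.18/0.88 = 7.4 points | 0.27 − 0.18 = 9.0 points |
| 50% | 0.45/0.95 − 0.30/0.80 = 9.9 points | 0.45 − 0.30 = 15.0 points |

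Swapping the arms reverses the sign. With q equal in both arms, the bias under no effect is 0.

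**5. Type I error**

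These figures come from exact enumeration at 12 per arm with the uncorrected chi-square test, two-sided 0.05.

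| p | Complete follow-up | Deleted, q 10% v 40% | Scored as non-progressor, q 10% v 40% |
|---|---|---|---|
| 30% | 4.9% | 6.8% | 7.0% |
| 50% | 6.4% | 8.0% | 13.0% |

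The 6.4% under complete follow-up reflects the test's small-sample behaviour, not these rules.

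**The case against.** The strongest reply is that this is a 24-subject exploratory phase I trial with a safety primary objective, and that the text is milder than it first looks. Several parts of that stand.

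- A reader might infer that 5.3 also contradicts intention-to-treat. It does not: a subject whose value is carried forward stays in the FAS. The fault lies in the value used.
- A reader might infer that 5.4 deletes patients because they do badly. The first two criteria are not outcome-based as written, and the third applies only where evaluation is judged impossible, so not every user of prohibited medication is excluded.
- A reader might infer from 8.1 that nothing but survival is followed after withdrawal. The section does not say so. It asks investigators to make every effort to have each subject complete follow-up, and Section 12.2 ties follow-up assessments to the flowchart. The text is ambiguous on efficacy data.
- A reader might infer that anyone who deteriorates or dies is scored as stable. Table 1 records exacerbation events on each of Days 1 to 8 and at every later visit, and an event recorded before withdrawal is not erased. The last assessment may itself show the decline. The protocol does not say whether death counts as progression.
- The direction of bias cannot be read from the documents. Section 5.1 admits varied conditions, including organizing pneumonia after COVID-19. If some of these patients improve, carry-forward understates their outcome.

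One defence fails. Reading 5.4 as a per-protocol rule does not reconcile the sections, because 5.4 speaks without restriction of the final and efficacy analyses, and 11.1 has its own PPS. The exploratory label does not help either, since 11.2 and 11.4 still plan significance tests between arms.

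**Conclusion.** The point holds in two parts. The conflict between 5.4 and 11.1/11.2 is a plain contradiction and needs no assumption. The carry-forward rule in 5.3 is a poor fixed choice because withdrawal may be tied to outcome and later values are discarded or may not be collected.

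Bias is a risk, not a demonstrated fact. It needs losses that differ between arms, and its sign depends on which arm loses more and on whether those subjects were worsening or improving. The 6 to 25 point range rests on the assumed 4/12 progressors per arm with one to three affected in one arm only. The type I error of 7% to 13% rests on assumed shares of 10% and 40% scored as non-progressors, at progression rates of 30% to 50%. It is also unclear whether the final analysis named in 5.4 includes safety, which matters for a trial whose primary objective is safety. Sections 5.4 and 11 need to be reconciled before any efficacy comparison is made.

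**What to change.** 1. In 5.4, state that the criteria define exclusion from the PPS only, and that all randomized subjects stay in the efficacy analysis under 11.1 and 11.2. Say that 5.4 does not remove anyone from the safety analysis, if that is the intent.
2. In 5.3, remove the carry-forward sentence as the main rule. Use all observed visits, and keep carry-forward at most as a sensitivity analysis. The particular model can be left to the statistical analysis plan.
3. In 8.1, state that subjects who stop treatment or leave early without withdrawing consent keep the remaining assessments scheduled in Table 1, not survival status alone.
4. In 11.4, state how death is counted in the progression endpoint.

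The cost is protocol wording and a few more visits by subjects who left early. Those visits are already scheduled, and since the treatment course is 7 days (Section 7.4), the Day 28 and Day 84 visits are off treatment for everyone.
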